#### Neonatal outcome

The primary neonatal outcome is a binary outcome indicating whether one of the following has occurred:

• Death

• Brain injury (defined as any intraventricular haemorrhage (IVH) (excludes subependymal haemorrhages), parenchymal cystic or haemorrhagic lesion or persistent ventriculomegaly (VI >97th percentile)

• Severe chronic lung disease (defined as need for ≥30% oxygen and/or positive pressure (positive pressure ventilation or nasal continuous positive airway pressure) at 36 weeks post menstrual age or discharge, which ever comes first).

The following null hypothesis will be tested: ‘There is no difference in the combined incidence of neonatal death, brain injury or severe chronic lung disease between the group treated with 200 mg / day progesterone and the group treated with placebo from week 22–24 to week 34 or earlier delivery’ This outcome is also compared between the treatment groups using a logistic regression model including treatment and previous pregnancy of at least 14 weeks. The hypothesis will be tested with a likelihood ratio test.

#### Childhood outcome

The primary childhood outcome is the Bayley III score, a continuous measure. This outcome will, by definition, not be available on babies who have died. Thus deaths need to be incorporated into the analysis, since the number of deaths may be sufficiently large as not to be negligible, and/or there may be a difference in the number of deaths between the two randomised groups. We will therefore use a two-stage statistical model that jointly models the treatment effect in both deaths and survivors [24], with deaths modelled using a binomial test and survivors modelled using a generalised linear model. The two parts are then combined to form the appropriate test statistic. Secondary analyses that adjust the estimated treatment effect for covariates felt to be of importance will be used as appropriate. Note that we will not be adjusting for gestational age in our analysis of childhood outcomes. The hypothesised mechanism of action of progesterone is to increase gestational age by reducing the proportion of women giving birth prematurely. To adjust for a post randomisation covariate (gestational age) which is a direct measure of the treatment effect, in a model that is estimating the consequence of that treatment effect (in terms of developmental outcome) is not statistically sound.

A fully detailed Statistical Analysis Plan will be prepared prior to unblinding.

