## Appendix

### Sample size calculations

#### Original sample size calculation based on data in the literature on the “fFN +” group

A sample size of 750 (375 per group) gives adequate statistical power to detect clinically important and plausible differences in the three primary measures of outcome. All these power calculations allow for loss to follow up rates and compliance. Delivery <34 weeks on placebo is expected to be 40% (data from an untreated high risk UK population with a positive fFN test at 22 weeks [27] and 27% on progesterone consistent with the odds ratio of 0.45 for the overall PTB with any progestational agent in the most recent systematic review [28]. With 750 randomised, the study will have 95% power at a 5% level of significance to detect such a reduction from 40% to 27% using a two-sided binomial test. For a more modest reduction from 40% to 30% (odds ratio 0.64) the study would still have 80% power. For the neonatal outcome, the Meis study found 7.2% died, 14.6% had CLD and 5.2% had IVH on placebo, compared to 4.6% death, 8.6% CLD and 1.3% IVH on progesterone [4]. Our neonatal primary outcome is a composite of these and also includes non-haemorrhagic brain injuries. With n = 750 randomised, the OPPTIMUM study would have 80% power at a 5% level of significance to detect a difference in this composite outcome of death, brain damage, or chronic lung disease from 20 to 12%, using a binomial test.

The childhood developmental outcome at 2 years will be assessed using the Bayley III Cognitive Scale which correlates well with later IQ. With 750 randomised, the study will have 93% power at a 5% level of significance to detect a difference in means equivalent to 0.25 of a standard deviations, using a two sample two sided *t*-test. Based on previous work [29], we estimate the standard deviation will be about 15 points, enabling us to detect a difference of 4 points in the Bayley Score. In clinical terms, a difference of 4 points is small, thus the power of the study to detect larger, more clinically significant differences, is high. We have powered this outcome at over 90% to make some allowance for a possible dilution of the power due to incorporating the deaths (using a two stage statistical model).

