There are no data yet on this outcome within OPPTIMUM. In the original calculation we assumed that the difference in mean Bayley score would be 4 units with a common standard deviation of 15 units. It is more difficult to assess the power convincingly with a mixture of fFN + and fFN- women on a continuous outcome such as the Bayley Score, since the power calculation requires assumptions about not just the anticipated treatment effect but also the assumed variability via the standard deviation. If we assume the same 4 unit difference in the fFN + and a 4/3 unit difference in the fFN- group (consistent with the pro-rata rate of delivery <34 weeks), with the same 15 unit standard deviation, then the study will have 71%, 73%, and 76% power if 1125, 1200, or 1275 are randomised (375:750, 400:800; and 425:850) as per Tables 1 and 2 above. However, this is for an unadjusted analysis, and in practice we will adjust for fFN + and fFN- group, and a limited number of other baseline covariates strongly related to Bayley Score at 2 years (e.g. gender) as specified in the statistical analysis plan, and this will reduce the variability and hence increase the power. For example, if the underlying variability in the lower risk group is lower – say halved, at 7.5 units, consistent with a higher proportion having uniformly high Bayley Scores since they have no disability – then the approximate power would be 93%, 94%, and 95% respectively for 1125, 1200, or 1275 randomised in total. In practice the reduction in variability by adjusting for both this design variate (fFN + and fFN- ) and additional baseline covariates may be considerably greater, so we are confident that the original power on the childhood development outcome will be protected at or above the original 90% level by randomising at least 1125 subjects (375:750).

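### The protocol conflicts on whether the primary childhood analysis is covariate-adjusted, and its claim of at least 90% power is not supported on either reading

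*Protocol article*

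**What the plan says.** **Methods, Childhood outcome.** The primary outcome is the Bayley III score. Deaths are handled by a binomial test and survivors by a generalised linear model, and the two parts are combined into one test. No covariate is named. The text continues: "Secondary analyses that adjust the estimated treatment effect for covariates felt to be of importance will be used as appropriate". It rules out adjusting for gestational age and promises a full analysis plan before unblinding.

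**Methods, Obstetric outcome and Neonatal outcome.** Both primary models are logistic regressions that name a covariate: previous pregnancy of at least 14 weeks.

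**Appendix, original calculation.** "93% power at a 5% level of significance to detect a difference in means equivalent to 0.25 of a standard deviations", with a "two sample two sided" *t*-test and 375 women per arm.

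**Appendix, revised calculation, childhood development outcome.** It assumes the "same 4 unit difference in the fFN + and a 4/3 unit difference in the fFN- group", and "with the same 15 unit standard deviation, then the study will have 71%, 73%, and 76% power if 1125, 1200, or 1275 are randomised". It labels these figures as belonging to an unadjusted analysis and continues: "in practice we will adjust for fFN + and fFN- group, and a limited number of other baseline covariates". The further covariates (gender is the example) are left to the analysis plan. It then gives 93%, 94% and 95% if the SD in fFN-negative women is 7.5, and concludes that 1125 women keep the power at 90% or more.

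**The concern.** The Methods put adjustment among the secondary analyses, so the primary survivor model appears to be unadjusted. The Appendix sets the unadjusted power aside because the analysis will be adjusted, and justifies 1125 women for this endpoint on that ground. An analysis-plan author could follow either section and cite the protocol for it.

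The stake is the stated power of one of three primary endpoints, and the one the trial describes as its distinctive contribution. If the Methods govern, a reader who takes the Appendix conclusion at face value expects 90% or more when the protocol's own figure is 71% to 76%. If the Appendix governs, it still has to be shown that adjustment can close that gap.

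**Working it through.** **Inputs from the Appendix.** Two-sided 5% level; 1:1 allocation; fFN-positive to fFN-negative ratio 1:2; effects of 4 and 4/3 points; SD 15, or 7.5 in fFN-negative women in the alternative scenario. No loss-to-follow-up rate is given and none is applied here.

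**Formula.** Power = Φ(δ / SE − 1.96), with SE = SD × √(4/N).

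**1. Original figure.** N = 750, δ = 0.25 × 15 = 3.75, SD 15: power 92.8%. Stated: 93%.

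**2. Unadjusted revised figures.** Average effect δ = (1 × 4 + 2 × 4/3) / 3 = 2.222 points. At N = 1125, SE = 15 × √(4/1125) = 0.894, δ/SE = 2.485, and Φ(0.525) = 70.0%.

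| N | Recomputed | Stated |
|---|---|---|
| 1125 | 70.0% | 71% |
| 1200 | 72.8% | 73% |
| 1275 | 75.3% | 76% |

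**3. The 93% to 95% scenario.** Average variance = (1 × 15² + 2 × 7.5²) / 3 = 112.5, so SD = 10.61. The same two-sample formula gives 94.0%, 95.2% and 96.3%, against the stated 93%, 94% and 95%. No covariate enters. A smaller SD in fFN-negative women would be a property of that population and would help the unadjusted test too. With the smaller SD and an assumed 8-point mean gap between fFN groups left unadjusted, variance is 112.5 + (2/9) × 64 = 126.7, and power at 1125 is still 91.2%.

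**4. What adjustment must deliver for 90%.** Required residual SD = 2.222 / ((1.960 + 1.282) × √(4/N)).

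| N | Residual SD needed | Share of variance explained, 1 − (SD/15)² |
|---|---|---|
| 1125 | 11.5 | 41% |
| 1200 | 11.9 | 37% |
| 1275 | 12.2 | 33% |

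At N = 1125, explaining 10%, 20%, 30% or 40% of the variance gives 74.5%, 79.3%, 84.4% or 89.4% power.

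**5. What fFN group and sex can plausibly deliver.** The document gives no covariate effects, so mean gaps are assumed. With a 1:2 split, an fFN gap D accounts for (1/3)(2/3)D² = (2/9)D² of the variance. With equal sexes, a sex gap g accounts for g²/4. Taking SD 15 as the total SD, at N = 1125:

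| fFN gap | Sex gap | Variance removed from 225 | Residual SD | Power |
|---|---|---|---|---|
| 3 | 3 | 2.00 + 2.25 = 4.25 (2%) | 14.86 | 71% |
| 5 | 5 | 5.56 + 6.25 = 11.81 (5%) | 14.60 | 72% |
| 10 | 5 | 22.22 + 6.25 = 28.47 (13%) | 14.02 | 76% |

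If SD 15 is instead the SD within fFN and sex groups, the adjusted analysis has 70.0% power whatever the gaps. The range is therefore about 70% to 76%.

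**The case against.** **The two sections might be compatible.** The Methods never call the primary model unadjusted and do not list the terms of the generalised linear model. The Appendix separates fFN group, as a design variable, from other covariates. One could read the primary model as carrying fFN group and terms named in the analysis plan, with the secondary analyses adding more. This is possible but strained: the obstetric and neonatal models name their covariate, the childhood model names none, and the next sentence calls adjustment secondary. The conflict stands, although it rests on that inference.

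**The covariate list is deferred.** This is right. Leaving the list to the analysis plan is no fault. The point is only whether adjustment is primary or secondary.

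**Selective reporting.** A reader might infer that the sponsor is free to report whichever result is favourable. The document does not support this: a full analysis plan is promised before unblinding, and the discretionary wording about important covariates governs secondary analyses only.

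**Power for the unadjusted test.** A reader might infer that the Appendix gives no power for the unadjusted analysis. It does, at 71% to 76%. Only its closing conclusion relies on adjustment.

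**Adjustment would not rescue the 90%.** This objection is correct and shapes the conclusion. Correcting the model alone would leave the power claim as unsupported as before. An unadjusted primary analysis with adjusted secondary ones would also be valid and would control the type I error.

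**Conclusion.** The concern holds as a conflict within the document together with an unsupported power conclusion. The Methods make adjustment secondary; the Appendix relies on it. Taken from the Methods, the primary childhood comparison has 71% to 76% power by the protocol's own figures (recomputed 70.0% to 75.3%). Adjustment for fFN group and sex would give about 70% to 76% at 1125 women under the assumed gaps. Reaching 90% there needs about 41% of the variance explained, or the separate assumption of a halved SD in fFN-negative women, which is not a result of adjusting.

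The stated power figures themselves reproduce to within 2 points, so the arithmetic is not at fault. The results rest on the protocol's effects and SD, no loss to follow-up, a plain comparison of survivor means rather than the combined two-part test, and mean gaps that are assumed because the document gives none. It would be too strong to conclude that the endpoint's type I error is compromised, or that adjusting the primary model restores 90% power.

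**What to change.** **Methods, Childhood outcome.** State that the survivor part of the primary two-stage model is adjusted for fFN group and child's sex, plus any other baseline covariates named in the analysis plan before unblinding. List the unadjusted model as a sensitivity analysis in place of the open-ended sentence on secondary adjustment. Keep the exclusion of gestational age at delivery.

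**Appendix, childhood development outcome.** Replace the conclusion of 90% or more with about 71% to 76% under SD 15 for 1125 to 1275 women. Present 93% to 95% only as conditional on an SD of 7.5 in fFN-negative women.

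If the sponsor prefers an unadjusted primary analysis, the Appendix sentence on adjustment should be brought into line, and the same power statement applies.

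**Cost.** One sentence in each place, before unblinding. fFN status is known from screening, and the Appendix already intends to use sex. No women, visits or data are added. The price is a less favourable stated power for this endpoint.

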### Planned subgroup analyses

In order to determine whether a reduced or improved response to progesterone can be predicted, subgroups of the ITT population will be formed according to the following factors:

• reason for risk of preterm delivery (spontaneous preterm birth yes / no and any preterm birth yes / no)

• previous pregnancy of at least 14 weeks (yes / no)

• cervical length at 18–24 weeks gestation (≤25 mm / >25 mm and ≤15 mm / >15 mm)

• chorioamnionitis diagnosed on pathology (yes / no)

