## Background, including rationale and any previous systematic review(s)

Preterm birth is a global problem, with a prevalence of 8 to 12% depending on location [1]. Around 75% of preterm birth follows spontaneous preterm labour, sometimes preceded by preterm premature membrane rupture [2]. Babies born preterm are at increased risk of a variety of adverse short term (neonatal) and long term complications, including neurodevelopmental disability. Women with a previous preterm birth (especially those women who delivered before 34 weeks following spontaneous preterm labour), women with a short cervix in early pregnancy [3], and women with a previous cone biopsy or laser loop excision to the cervix [4] are at all at increased risk of spontaneous preterm birth.

Several large trials and meta-analyses have shown progesterone to be effective in preventing or delaying preterm birth in selected high risk women (short cervix or previous preterm birth) with singleton pregnancy [5-11]. There is data that both intramuscular 17 hydroxyprogesterone caproate and vaginal progesterone are effective in preventing preterm birth. OPPTIMUM likewise is investigating the efficacy of progesterone in women at elevated risk of preterm birth, but will crucially address longer term childhood developmental outcomes.

Although an improvement in short term neonatal outcomes has been shown in some trials [6-8] these have not consistently been confirmed in meta-analyses [9,10]. Data on longer term outcomes in singletons is limited to follow up of babies of women in the Meis trial, where 80% of babies were assessed by questionnaire at a mean age of four years. No differences in childhood outcomes were demonstrated, despite the progesterone group having a lower incidence of preterm birth [12].

The mechanisms of action of progesterone are somewhat uncertain although a direct inhibitory effect on the processes of parturition seem likely [13]. Additionally progesterone could exert anti-inflammatory properties [13] and/or direct CNS protective effects [14], which could help to reduce the risk or severity of long term neonatal problems.

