If the prevention of preterm birth is accompanied by a reduction in the complications of prematurity, then *in utero* progesterone should be predicted to have long term beneficial effects. Harmful long term effects are however also possible. Although direct teratogenic effects of progesterone are unlikely, there could be adverse effects of keeping the fetus in utero in a compromised intrauterine environment where infection or inflammation is present. Caution is therefore warranted before progesterone use becomes widespread, particularly since drugs (including antibiotics and estrogens) thought to be beneficial in women at risk of preterm birth have now been demonstrated to have long term adverse effects [15-17].

The OPPTIMUM study is designed to determine whether progesterone prophylaxis to prevent preterm birth has long term neonatal or childhood benefit. Specifically it will study whether, in women at elevated risk of preterm labour, prophylactic vaginal natural progesterone, 200 mg (compared to placebo), daily from 22 – 24 weeks up to 34 weeks gestation, improves obstetric outcome by lengthening pregnancy thus reducing the incidence of preterm delivery (before 34 weeks), improves neonatal outcome by reducing a composite of death and major morbidity and leads to improved childhood cognitive and neurosensory outcomes at two years of age.

The OPPTIMUM study began recruiting in January 2009. Since then, one large, and several other smaller studies have reported the effect of progesterone, either as vaginal progesterone or as intramuscular 17 hydroxyprogesteronecaproate. None fully addresses the crucial question regarding long term outcome (childhood development at 2 years). Additionally, we note that the US Food and Drug Administration (FDA) has indicated that long term childhood outcome data are required to determine the clinical benefits and risks of 17 hydroxyprogesteronecaproate for the prevention of preterm birth in women with a previous preterm birth._._^a^ An FDA panel also recently ruled that data supplied on vaginal progesterone gel “do not [yet] support the efficacy of progesterone gel compared with placebo in reducing the risk of preterm births before 33 completed weeks of gestation among women with a short cervical length”.^b^ We believe that OPPTIMUM will address these important evidence gaps about the efficacy of vaginal progesterone and any childhood effects of progestogens in general.

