#### Obstetric outcome

The primary obstetric outcome is delivery or fetal death before 34 completed weeks of gestation based on ultrasound (based on the projected date of delivery estimated from scan in the first trimester). The following null hypothesis will be tested: ‘There is no difference in the incidence of delivery or fetal death before 34 completed weeks of gestation between the group treated with 200 mg / day progesterone and the group treated with placebo from week 22–24 to week 34 of gestation or earlier delivery’.

The outcome is compared between the treatment groups using a logistic regression model including treatment and previous pregnancy of at least 14 weeks. The hypothesis will be tested with a likelihood ratio test.

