#### The revised sample size calculation below, based on blinded data (as of April 2011) and inclusion of the "fFN"- group is around 1250 participants

**Obstetric outcome** (delivery <34 weeks).

The table below gives the estimated power for three combinations of sample size (all 1:2 fFN+/fFN- groups, assuming 375:750 (total 1125), 400:800 (total 1200) and 425:850 (total 1275) assuming (fFN+, fFN-) event rates (delivery < 34 weeks) of (40%, 10%), (45%, 13%), and (45%, 15%). All calculations assume a relative treatment effect of 32.5%.

The justification for these combinations is as follows:

1. The 40% untreated rate is as per the original assumption. We have looked at the blinded (aggregated) event rate for the first 67 women randomised in OPPTIMUM (ignoring any possible bias created by recording the early births before later births in the most recently randomised). For the fFN + group, 29/67 (43%, 95% exact confidence interval 31% to 56%) had delivered at <34 weeks. The blinded event rate according to the assumed 40% untreated rate with a 27% treated rate (32.5% relative reduction) would be 33.5%. Although the numbers are relatively small, there appears to be a higher event rate than anticipated, which would be consistent with having selected a higher risk and hence scarcer subset than we planned for). An overall blinded rate of 43% could comprise an untreated rate of 52% and a treated rate of 35%. We assume conservatively that the baseline event rate in the untreated fFN + group is 45%.

2. For the fFN- group women data on the first 24 women suggested that 8/24 (33%, exact 95% confidence interval 16% to 55%) had delivered early. As indicated above, this percentage is likely to be inflated since we record the early deliveries before observing the term deliveries. However, fortunately, we also had followed up those who were not randomised (by definition, all of whom had a negative fFN test) into OPPTIMUM from the start. Of the 398 followed, 32 have had a delivery <34 weeks. We know that 57% of these 398 would have been eligible for the trial (short cervix < 25 mm), and the epidemiology indicates that it is very unlikely to give birth <34 weeks with none of the classic risk factors. So we conservatively estimate that around 13% (i.e. around 29/225, exact confidence interval 9% to 18%) of those recruited into the fFN- group, based on OPPTIMUM data, will have a delivery <34 weeks.

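### Chorioamnionitis on pathology is listed as a factor for predicting response, but it is diagnosed after treatment and treatment may change it, so its strata are not randomised comparisons

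*Protocol article*

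**What the plan says.** Under Planned subgroup analyses, the protocol article gives the purpose and population: "In order to determine whether a reduced or improved response to progesterone can be predicted, subgroups of the ITT population will be formed". Four factors follow. Three are obstetric history or cervical length at 18 to 24 weeks, so they are fixed before randomisation or measured around it. The fourth is "chorioamnionitis diagnosed on pathology (yes / no"). It carries no caveat, no exploratory label and no separate status.

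Other sections bear on this factor:

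- **Obstetric outcome:** treatment runs from week 22–24 until "week 34 of gestation or earlier delivery".
- **Background:** "Additionally progesterone could exert anti-inflammatory properties". The same section warns that "there could be adverse effects of keeping the fetus in utero in a compromised intrauterine environment where infection or inflammation is present".
- **Childhood outcome:** the plan declines to adjust for gestational age. It calls the following step statistically unsound in a model of the consequences of treatment: "To adjust for a post randomisation covariate (gestational age) which is a direct measure of the treatment effect".

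**The concern.** There are two separate difficulties.

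1. **Purpose.** A predictor of response has to be known when the decision to treat is made. A pathology finding made after delivery is not, so the factor cannot do what the section asks of it. This holds even if the subgroup estimates are free of bias.
2. **Validity.** If progesterone changes who is classed as having chorioamnionitis, the women classed positive on progesterone are a different kind of women from those classed positive on placebo. The same holds for those classed negative. The comparison within a stratum then mixes the effect of treatment with a difference in case mix.

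The Background section names infection or inflammation as the setting in which progesterone might do harm. Readers would take this subgroup as the test of that worry, and it could create or hide a difference that the trial has not shown.

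**Working it through.** The plan states no figure for this point, so there is none to reproduce. The check is one of timing and logic, followed by two illustrations of size.

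**Timing.** Capsules start at 22 to 24 weeks and continue to 34 weeks or earlier delivery. Pathology of the trial pregnancy's placenta and membranes follows delivery, so the factor is observed after treatment.

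**Routes from treatment to the factor.** The Background section supplies two: a possible anti-inflammatory action, and a longer stay in an infected or inflamed environment. The first would make chorioamnionitis less frequent and the second could make it more frequent. The direction is therefore open.

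**Illustration A (all inputs assumed).** Suppose 70% of women have no inflammation (20% deliver early), 15% have mild inflammation (30%) and 15% severe (70%). Treatment clears the mild histology and changes no delivery.

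- Early delivery in both arms: 0.70×0.20 + 0.15×0.30 + 0.15×0.70 = 0.29.
- Positive stratum, placebo: (0.15×0.30 + 0.15×0.70)/0.30 = 50%. Progesterone: severe cases only, 70%.
- Negative stratum, placebo: 20%. Progesterone: (0.70×0.20 + 0.15×0.30)/0.85 = 21.8%.

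Both strata show apparent harm although the two arms have identical overall risk.

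**Illustration B (exact probabilities, different assumed inputs).** Latent inflammation U has prevalence 0.30. Early delivery on placebo has probability 0.12 without U and 0.45 with U. Chorioamnionitis C has probability 0.05 without U and 0.50 with U. In some rows 0.30 is added to P(C) after early delivery. Treatment multiplies P(C) by 1, 0.75 or 0.5. The true relative risk (RR) for delivery is the same at both levels of U: either 1, or 1 − 0.325 = 0.675, the relative effect in the protocol's revised sample size calculation. That 0.675 is the only input taken from the document.

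One row by hand (true RR 1, no added link, P(C) halved), negative stratum:

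- Placebo: (0.70×0.95×0.12 + 0.30×0.50×0.45)/(0.70×0.95 + 0.30×0.50) = 0.1473/0.815 = 0.181.
- Progesterone: (0.70×0.975×0.12 + 0.30×0.75×0.45)/(0.70×0.975 + 0.30×0.75) = 0.18315/0.9075 = 0.202.
- RR = 0.202/0.181 = 1.117 from unrounded values.

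All rows, with RR and odds ratio (OR) by stratum:

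| True RR | Added to P(C) after early delivery | Treatment multiplies P(C) by | RR, C positive | RR, C negative | OR, C positive | OR, C negative |
|---|---|---|---|---|---|---|
| 1 | 0 | 1 | 1.000 | 1.000 | 1.000 | 1.000 |
| 1 | 0 | 0.75 | 1.000 | 1.061 | 1.000 | 1.076 |
| 1 | 0 | 0.5 | 1.000 | 1.117 | 1.000 | 1.146 |
| 1 | 0.30 | 1 | 1.000 | 1.000 | 1.000 | 1.000 |
| 1 | 0.30 | 0.75 | 1.000 | 1.311 | 1.000 | 1.363 |
| 1 | 0.30 | 0.5 | 1.000 | 1.578 | 1.000 | 1.698 |
| 0.675 | 0 | 1 | 0.675 | 0.675 | 0.560 | 0.630 |
| 0.675 | 0 | 0.75 | 0.675 | 0.716 | 0.560 | 0.674 |
| 0.675 | 0 | 0.5 | 0.675 | 0.754 | 0.560 | 0.715 |
| 0.675 | 0.30 | 1 | 0.738 | 0.656 | 0.560 | 0.630 |
| 0.675 | 0.30 | 0.75 | 0.738 | 0.868 | 0.560 | 0.854 |
| 0.675 | 0.30 | 0.5 | 0.738 | 1.052 | 0.560 | 1.059 |

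Three things follow:

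- With no effect of treatment on C by any route, nothing is distorted. The RRs are 1 and 1, or 0.675 and 0.675. The ORs of 0.560 and 0.630 in that last case only reflect a constant RR at different baseline risks.
- With a direct effect on C, the negative stratum is distorted on both scales.
- When treatment reaches C only by preventing early delivery (true RR 0.675, 0.30 added, multiplier 1), the RRs separate to 0.738 and 0.656, but the ORs are the same as without that link. The planned primary obstetric model is logistic, so this last route should not be leaned on.

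**The case against.** Much can be said for the plan, and several stronger readings fail.

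- **A reader might infer that these subgroup effects are certainly biased.** The documents do not support that. The Background section says only that progesterone could act on inflammation and calls its mechanisms uncertain. If treatment does not touch chorioamnionitis or its detection, there is no bias.
- **A reader might infer false harm in the inflamed group specifically.** Illustration A shows it there. Illustration B with no true effect leaves the positive stratum at 1.00 and distorts the negative one. Size and location depend on the assumed inputs, so these figures show what is possible and are not an estimate for this trial.
- **A reader might say that the plan forbids this very step elsewhere.** It does not quite. The objection to gestational age concerns covariate adjustment of the childhood outcome, and gestational age is a direct measure of the treatment's action. Chorioamnionitis is a possible consequence of treatment, used to split subgroups. The reasoning carries over by analogy.
- **Some premises are inferred.** The specimen is not named, so diagnosis after delivery is the natural reading and not a stated fact. The article does not itself say that chorioamnionitis goes with early delivery.
- **The question is a fair one.** The Background section gives a scientific reason to look at infection and inflammation, and the full analysis plan, still to be written before unblinding, could label the analysis suitably.

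These points limit the claim but do not remove it. The factor stands without caveat in a list whose stated aim it cannot serve, and the protocol itself supplies the reasons to doubt the comparison within strata.

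**Conclusion.** The point holds in limited form. As a predictor of response the factor fails on timing alone. As a subgroup factor it gives contrasts that randomisation does not protect and that are open to bias of unknown size and direction. In Illustration B with no true effect, the RR in the negative stratum runs from 1.00 (no effect on chorioamnionitis) to 1.58 (chorioamnionitis halved and also commoner after early delivery).

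This rests on two assumptions: that the pathology is that of the trial pregnancy, and that progesterone may alter chorioamnionitis or its detection, which the Background section makes plausible but does not establish. The choice also sits badly with the plan's own reasoning on gestational age.

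Severity is moderate. The primary analyses do not use the factor, and no sample size, significance level or primary conclusion depends on it.

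**What to change.** Make the change before unblinding, both in the protocol's Planned subgroup analyses and in the statistical analysis plan:

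1. Remove chorioamnionitis from the factors used to predict response, and keep only factors fixed at baseline.
2. Report chorioamnionitis by arm as a post-randomisation outcome.
3. If an analysis stratified by it is still wanted, label it exploratory and non-causal, and state that the strata are not randomised groups.

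Fetal fibronectin at 22 weeks should not be substituted as a baseline marker of inflammation on the strength of these documents, which use it only to screen for risk of preterm birth.

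The cost is a wording change in two documents. One subgroup table becomes a descriptive outcome table; no new data, sample size or primary analysis is involved.
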